**Methods and analysis:**

This is a multi‐centre observational study involving sites across the UK. Recruitment is over a 6‐year period (2019–2025). Patients recruited to the study are those attending for colonoscopy. Patients are recruited into two groups, namely observational group A (10 000 patients) and C4C group B (10 000 patients), known as COLO‐SPEED (Colorectal Cancer Screening Prevention Endoscopy and Early Diagnosis; https://colospeed.uk). Patients complete a health questionnaire, provide anthropometric measurements and submit biosamples (blood and stool—depending on the part of the study they are recruited into). Patients' colonoscopy and histology findings are also recorded. Models of factors associated with the presence of neoplasia at colonoscopy will be developed using logistic or multinomial regression. For internal validation, model discrimination and calibration will be assessed and bootstrapping and cross‐validation approaches used. To enable long‐term follow‐up for outcomes related to colorectal cancer and polyps, patients are asked to consent to follow‐up through data linkage with national databases.

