### Statistical analysis and sample size

Data from patients recruited to group A will be used to develop the risk prediction model. Primary analysis will be based on the outcome of the presence of colorectal neoplasia at the recruitment colonoscopy. This will be defined as the presence of advanced adenoma (AA)/CRC. AA will be defined as an adenoma of at least 10 mm in size or containing high‐grade dysplasia [38]. Secondary analyses will focus on other relevant outcomes, including CRC (only), AA (only), any adenoma, any polyp, serrated polyps, numbers of adenomas and number of polyps. The TRIPOD statement will be followed for reporting of the risk prediction model [39].

Initially we will develop models separately for BCSP and other (mainly symptomatic) subjects; further analysis will explore whether an overall model can be created. Firstly (in the non‐BCSP subjects), sensitivity, specificity, positive predictive value and negative predictive value of FIT alone for the detection of the presence of AA/CRC will be assessed. Different FIT cut‐offs will be explored. Subsequently, the relationship between patient characteristics and lifestyle, phenotypic information, FIT results, blood markers and presence of AA/CRC will be investigated using logistic regression. Backwards elimination of candidate predictors will be used to identify variables which best predict neoplasia [40]. Receiver operating curve plots, area under the curve analyses of sensitivity and specificity, and Harrell's C‐index will be used to characterize the discriminative ability of the models [41, 42]. Calibration will be assessed using Hosmer and Lemeshow tests, the percentage of people reclassified by different models and the net reclassification index [43]. Internal validation will be undertaken using bootstrapping to quantify the model's potential for overfitting and optimism in estimated model performance [40]. Cross‐validation approaches will also be applied, systematically excluding groups of subjects (e.g., by site) in turn [44]. In addition, multinomial, or ordinal, logistic regression will be used to investigate predictors of the secondary outcomes. Multiple adenomas may occur in an individual. It is anticipated that the presence of multiple adenomas will be zero‐inflated, with some patients having zero and others many. The extent to which zero‐inflated models (e.g., allowing for aggregation) improve the prediction of the presence of adenomas will be assessed.

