The microbiome data will be subjected to canonical correspondence analysis to identify (i) major trends in variation across the patient cohort and (ii) putative drivers of the variation in each patient subgroup (defined on the basis of colonoscopy result: CRC, advanced adenomas, non‐advanced adenomas, sessile serrated polyps and clear colon). Canonical correspondence analysis seeks to explain the pattern of variation in complex (multivariate) datasets using covariates hypothesized to be of significance in causing variation. We hypothesize that there will be differences in microbiome composition that will be dependent on the adenoma/disease status of patients and that these may act as markers for disease. We will use similar approaches to determine whether dietary data, when combined with the microbiome, reveal further differences between groups. Correspondence analysis will be used to provide summaries of the variation microbiome to allow for investigation of the contribution of microbiota profile to the risk prediction models.

The study is exploratory in nature—particularly in relation to whether microbiome data make an important contribution to risk prediction models. Therefore the sample size calculation must be governed by principles of adequate population size.

The sample size of patients providing biosamples (6000) is based on the power calculation by Peduzzi et al. [45]: sample size *N* = 10(*k*/*p*), where *k* is the number of covariates to be investigated in the model and *p* is the smallest of the proportions of positive or negative cases.

Using Demidenko's method, the sample size needed for logistic regression with 80% power and 5% level of significance is *N* = 8*V*/*β*2, where *β* is the natural log of the odds ratio and *V* is logistic model variance due to covariates [46]. This formula can be rearranged to determine the minimum odds ratio that can be detected at a sample size of 6000 with sufficient power. Assuming a moderate standard error in the regression (SE = 0.125) and calculating *V* from the standard error (*V* = (SE√*N*)2) the study will have sufficient statistical power to detect an effect with a small effect size with an odds ratio of 1.13.

Group B sample size is based upon generating a significant but manageable C4C population.

A full statistical analysis plan will be developed prior to data analysis.

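### Two of the three measures named for calibration do not measure it, and the third, the Hosmer-Lemeshow test, shows neither the size nor the direction of miscalibration

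*Protocol article*

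**What the plan says.** All of this stands in the Protocol article, mostly under Statistical analysis and sample size. Discrimination gets its own measures: ROC plots, "area under the curve analyses of sensitivity and specificity, and Harrell's C" index. The next sentence turns to calibration and names three measures: "Calibration will be assessed using Hosmer and Lemeshow tests, the percentage of people reclassified by different models and the net reclassification index". Validation follows: "Internal validation will be undertaken using bootstrapping to quantify the model's potential for overfitting and optimism in estimated model performance", together with cross-validation that leaves out groups of subjects, for example sites, in turn. On reporting, "The TRIPOD statement will be followed for reporting of the risk prediction model". The abstract also promises calibration as part of internal validation: "For internal validation, model discrimination and calibration will be assessed and bootstrapping and" cross-validation used.

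On the data: "Data from patients recruited to group A will be used to develop the risk prediction model", which means 10 000 people, 6000 of them with biosamples (A1) and 4000 without (A2). They are first split: "Initially we will develop models separately for BCSP and other (mainly symptomatic) subjects". The sizes of those two strata are not given.

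**The concern.** Calibration asks whether people given a predicted risk of, say, 10% have the outcome about 10% of the time. Percentage reclassified and the NRI ask how people move between two models' predictions. The sentence therefore gives two of its three places to measures of something else.

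The remaining measure is a significance test. It does not say whether risks are too high, too low or too extreme, nor by how much, and its power depends on sample size and prevalence. Both will probably differ between the screening and non-screening models.

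The Discussion intends the model, after external validation, to direct colonoscopy towards people at highest risk and away from those at low risk. The size of error in absolute risk bears on that use, and none of the named measures reports it.

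**Working it through.** The article states no calibration figure, so there is nothing to reproduce. The checks below are simulations. Prevalence of advanced adenoma or cancer (10 to 30%), the spread of the linear predictor and the risk cut-offs (5%, 10%, 20%) are assumptions, because the article gives none.

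**1. Does reclassification register miscalibration?**

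With up and down meaning a higher or lower risk (or risk category) under the second model, NRI = [P(up | event) − P(down | event)] + [P(down | non-event) − P(up | non-event)].

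For the category-free version the answer follows from algebra. Doubling the odds in both models adds ln 2 to both logits, so the sign of each person's change, and hence the NRI, stays the same. Doubling the odds in the second model only, with ranks unchanged, moves everyone up: events contribute +1, non-events −1, total 0.

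One million simulated subjects, true logit = a + 1.0·x1 + 0.6·x2, prevalence 15%. Model A uses x1 only; model B is the true model.

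| Comparison | Observed/expected | Reclassified | Categorical NRI | Category-free NRI |
|---|---|---|---|---|
| A to B, both calibrated | 1.00 and 1.00 | 41.6% | +0.19 | +0.46 |
| A to B, odds doubled in both | 0.61 and 0.63 | 35.6% | +0.18 | +0.46 |
| B to B with odds doubled | 1.00 and 0.63 | 58.7% | −0.26 | 0.00 |
| B to overfitted B (slope 0.70, same ranks) | 1.00 and 0.81 | 14.1% | +0.07 | +0.77 |

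Rows 1 and 2 give nearly the same NRI for a sound pair and a badly miscalibrated pair. Row 4 rewards the worse-calibrated model although AUC is 0.777 for both. Row 3 shows that miscalibration can move the categorical NRI and the percentage reclassified, but neither separates it from a change in predictive value. At 10% and 25% prevalence rows 1 and 2 again have identical category-free NRIs, and row 4 again favours the miscalibrated model.

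**2. How does Hosmer-Lemeshow behave as n changes?**

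The statistic sums (O − E)²/[n_g·p_g(1 − p_g)] over 10 risk groups. If group g's predicted risk is off by d_g, its term has expectation of about 1 + n_g·d_g²/[p_g(1 − p_g)]. The excess grows in proportion to n and vanishes only when every d_g is zero.

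Percentage of 1000 runs rejecting at 5% (linear predictor SD 1, fixed predictions as in held-out data, chi-square with 10 df):

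| Slope, prevalence | 500 | 1000 | 2000 | 4000 | 6000 | 10 000 | 20 000 |
|---|---|---|---|---|---|---|---|
| 1.00, 15% | 4.7 | 4.3 | 6.2 | 5.9 | 5.2 | 3.4 | 7.2 |
| 0.85, 10% | 13.1 | 20.0 | 27.5 | 45.2 | 64.6 | 86.9 | 99.7 |
| 0.85, 15% | 15.2 | 20.6 | 35.3 | 62.4 | 78.6 | 95.2 | 100 |
| 0.85, 30% | 15.5 | 26.1 | 43.6 | 76.7 | 92.5 | 99.3 | 100 |

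Illustration, with an assumed split of the 6000 into 2000 and 4000 at 15% prevalence: the same slope of 0.85 is rejected in 35% of runs in one stratum and 62% in the other. At equal size (4000), moving prevalence from 10% to 30% changes rejection from 45% to 77%. A pass in one stratum and a failure in the other would not show that one model is better calibrated.

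**3. Does the test see overfitting in development data?**

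Maximum-likelihood logistic regression satisfies Σ(y − p̂) = 0 and Σx_j(y − p̂) = 0 for each predictor, hence Σ(linear predictor)(y − p̂) = 0. Recalibrating in the same data returns intercept 0 and slope 1 whatever the degree of overfitting, so the test has little to find. In a stress case (N = 1000, 40 candidate predictors, 4 informative, 200 runs) it rejected in 2% of runs while the true slope averaged 0.52. Other fitted models with true slopes from 0.59 to 0.91 gave 4 to 6% rejection.

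Wrong functional form is different. With a mild omitted quadratic term, in-sample rejection was 7% at n = 500 and 1000, 14% at 2000, 49% at 6000 and 75% at 10 000.

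**The case against.** **This is a condensed article and an analysis plan is promised.** True, and the absence of a plot, slope or intercept would not by itself be a finding. The point rests on the sentence that positively assigns reclassification measures to calibration; a later plan would have to correct it. TRIPOD is cited for reporting and does not change what the named measures measure.

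**Bootstrapping and cross-validation are planned.** They correct whatever is measured. Run on held-out sites, Hosmer-Lemeshow could respond to overfitting, but it would still return a p-value driven partly by site size.

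**Serious overfitting is unlikely at these sizes.** This largely stands. With 13 predictors, the true slope averaged about 0.97 at N = 3000 (95% of runs 0.85 to 1.13), 0.96 at 6000 and 0.84 at 1000. At 10 000 the test would reject a slope of 0.8 almost always in held-out data. A reader might infer that the study is set to certify an overfitted model as well calibrated; the article does not support that, although a small stratum remains exposed.

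**Uninformative microbiome scores would earn a positive NRI.** A reader might infer this too. Five noise variables forced in at N = 3000 gave an apparent category-free NRI of about +0.12. That is not what the article plans. Bootstrap correction brought it to about +0.04 (95% of runs −0.06 to 0.14), against +0.01 in new data, and backwards elimination (at an assumed p < 0.05) removed all five in 75% of runs. The figure does not predict this study's result.

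**Triage harm.** A reader might infer that fixed risk thresholds will act directly on these predictions. The article states no threshold and places clinical use after external validation.

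**Reclassification tables can compare observed with predicted risk within cells.** They can, but the article names only the percentage and the index.

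**Conclusion.** The concern holds as a misstatement of method. Percentage reclassified and NRI are not calibration measures, so Hosmer-Lemeshow is the only one named. It is a genuine but weak one: no size, no direction, a rejection rate for slope 0.85 that runs from 13–16% at n = 500 to 87–99% at 10 000 (prevalence 10 to 30%), and little sensitivity to overfitting in development data.

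Two limits apply. The dependence on sample size arises only when some miscalibration exists; under perfect calibration rejection stayed at 3 to 8% across all settings, with no trend in n. Nor is the test satisfied automatically in development data, since it does pick up a wrong functional form at large n.

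The percentages rest on the assumed prevalence, predictor spread and cut-offs. That the category-free NRI ignores a common shift in odds, and that in-sample recalibration returns slope 1, do not. Importance is moderate: the point affects how the main model is judged, and it can be settled before any analysis.

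**What to change.** Replace the calibration sentence in the analysis plan along these lines: calibration will be assessed by a smoothed calibration plot, calibration-in-the-large (intercept or observed/expected ratio) and the calibration slope, for the screening and non-screening models separately. Each will be corrected for optimism with the planned bootstrap, repeating the backwards elimination in every resample, and reported for each held-out site in the planned cross-validation. The correction is essential, because the uncorrected slope in development data is 1 by construction.

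Keep Hosmer-Lemeshow as a secondary result at most. Move percentage reclassified and NRI to a sentence on comparing models, for example against FIT alone, optimism-corrected and shown separately for events and non-events.

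The cost is a change of wording and standard code. No new data, sample size or recruitment change is needed.

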### Data collection

#### Group A

Six thousand participants in group A (group A1) will submit a pre‐bowel preparation FIT sample. This will be a combination of new FIT collections and samples from patients who have already submitted a FIT sample as part of the BCSP (Figure 1).

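### Zero-inflated count models are to be judged on presence of adenomas, a yes/no outcome on which they can gain almost nothing, rather than on the number of adenomas

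*Protocol article*

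**What the plan says.** All the text is in the section Statistical analysis and sample size of the protocol article. The secondary outcomes include "any adenoma, any polyp, serrated polyps, numbers of adenomas and number of polyps", so any adenoma (yes/no) and the number of adenomas (a count) are separate outcomes. For the secondary outcomes in general, multinomial or ordinal "logistic regression will be used to investigate predictors of the secondary outcomes".

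The section then turns to patients with several adenomas. "It is anticipated that the presence of multiple adenomas will be" zero-inflated, it says, "with some patients having zero and others many". How far zero-inflated models "improve the prediction of the presence of adenomas will be assessed", it concludes. A parenthesis just before these words ("e.g., allowing for aggregation) improve the prediction of the presence of adenomas") shows that overdispersion was considered, as an example of what a zero-inflated model might include.

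**The concern.** There are two mismatches.

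1. **Criterion.** A zero-inflated model is a model for a count. Its purpose is to describe how many adenomas a patient has when there are more zeros than the count distribution allows. The article scores it on presence, which discards everything beyond zero against non-zero. Logistic regression already models that contrast directly.
2. **Rationale.** A mixture of patients with none and patients with many does not by itself point to zero inflation. A negative binomial with no separate class of structural zeros produces the same pattern. Aggregation is mentioned only as an option within the zero-inflated family, so the text does not set the simpler explanation against the more complex one.

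At stake is whether this secondary analysis can answer a useful question. A finding of no gain for presence could be taken to mean that zero inflation is absent or unhelpful, when the number of adenomas had not been examined on that question.

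**Working it through.** The plan gives no figure on this point, so there is none to reproduce. It also gives no adenoma prevalence, mean count or dispersion. All the inputs below are assumptions except the size of 6000, which is that of group A1 ("Six thousand participants in group A (group A1) will submit").

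**Step 1. Does the described pattern imply zero inflation?** For a negative binomial with mean μ and dispersion parameter k, and no structural zeros, P(0) = (k/(k+μ))^k. For a Poisson, P(0) = exp(−μ). With μ = 1 and k = 0.5, P(0) = (0.5/1.5)^0.5 = 57.7%, against exp(−1) = 36.8%. Over a range (negative binomial share with zero / share with five or more):

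| Mean | Poisson zeros | k = 0.3 | k = 0.5 | k = 1 |
|---|---|---|---|---|
| 0.5 | 60.7% | 74.5% / 1.7% | 70.7% / 1.0% | 66.7% / 0.4% |
| 1 | 36.8% | 64.4% / 6.1% | 57.7% / 4.9% | 50.0% / 3.1% |
| 2 | 13.5% | 54.3% / 14.4% | 44.7% / 14.5% | 33.3% / 13.2% |

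Many zeros together with some high counts arise without any zero inflation. The pattern does not rule zero inflation out either; it does not separate the two.

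**Step 2. What can a count model add for presence?** A hurdle model's likelihood splits into a binary part for zero against non-zero and a part for the positive counts. With a logit link the binary part is the logistic regression, so the gain for presence is exactly nil. A zero-inflated negative binomial gives P(Y>0) = (1−π)[1 − (1+αμ)^(−1/α)], with π the structural-zero probability and α = 1/k. It can borrow some information from the counts, so the gain can be small rather than nil.

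**Step 3. How small?** The simulation used 8 covariates with assumed effects, 10 replicates and 40,000 test patients per replicate. Prevalence of any adenoma came out at 0.32 to 0.39. AUC for any adenoma in the test data:

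| True model | n | Logistic | Zero-inflated negative binomial | Zero-inflated Poisson |
|---|---|---|---|---|
| Zero-inflated negative binomial | 1000 | 0.6964 | 0.6945 | 0.6962 |
| Zero-inflated negative binomial | 6000 | 0.6994 | 0.6994 | 0.6993 |
| Hurdle negative binomial | 1000 | 0.6606 | 0.6574 | 0.6591 |
| Hurdle negative binomial | 6000 | 0.6681 | 0.6667 | 0.6671 |
| Plain negative binomial | 1000 | 0.6324 | 0.6275 | 0.6324 |
| Plain negative binomial | 6000 | 0.6376 | 0.6366 | 0.6376 |

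To four decimals, no zero-inflated model exceeded logistic regression in any row. In the case most favourable to the plan (zero-inflated truth, n = 6000), log-loss was 0.5680 for logistic and 0.5678 for the zero-inflated negative binomial, a difference of 0.0002. The only count model to gain on presence was the plain negative binomial when it was the truth (0.6370 against 0.6324 at n = 1000; 0.6381 against 0.6376 at n = 6000), and that gain owes nothing to zero inflation. Some zero-inflated fits gave convergence warnings, so their log-loss under plain negative binomial truth is not relied on.

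**Step 4. Does the count reveal what presence hides?** In a separate simulation of truly zero-inflated negative binomial data (n = 6000, assumed inputs), presence AUC was 0.640 for both the logistic and the zero-inflated model. On the counts, the zero-inflated model beat the plain negative binomial by about 54 log-likelihood units in sample, and it was also better out of sample. In plain negative binomial data (n = 6000), the zero-inflated version, with a constant inflation term, added about 1 unit (−7593 against −7594). The two runs used different inputs, but the contrast is clear: scored on the count, the comparison responds to zero inflation; scored on presence, it hardly does.

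**The case against.** The strongest reply is that one loosely worded, exploratory sentence is being read literally. The sentences around it speak of several adenomas in one patient and of none against many, which is a count, so presence may simply stand for number. That may well be the intent, but the wording should then be corrected, because a later analysis plan that follows it would inherit the wrong target.

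Other replies stand, and they limit the point:

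- **The comparator.** The article promises a full statistical analysis plan before analysis. That no plain negative binomial is named is not by itself a fault in an article.
- **Overdispersion mistaken for zero inflation.** A reader might infer this. The text does not support it: aggregation is mentioned, zero inflation is only anticipated, and the described pattern fits either explanation.
- **A spurious adenoma-free class.** A reader might also infer that the plan will find one. That danger is real when a zero-inflated Poisson is set against a Poisson in overdispersed data, but the article proposes no Poisson model and draws no two-class conclusion.
- **No usable analysis of the count.** This goes too far, since multinomial or ordinal regression is named for the secondary outcomes.
- **An assessment that cannot give an answer.** It can: little or no gain is a legitimate result. The difficulty is that this result is predictable and concerns the wrong outcome.

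**Conclusion.** The point holds in a limited form. The stated criterion is close to blind to what zero-inflated models are for. Under the assumed inputs they gained nothing in AUC and at most about 0.0002 in log-loss on presence in truly zero-inflated data, so the assessment as worded is near-certain to be null and would say little about the number of adenomas. The reason offered for expecting zero inflation does not distinguish it from overdispersion.

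The conclusion for the hurdle model and the closed-form result follow from model structure. The other sizes depend on assumed means, dispersion and covariate effects. The sizes of 1000 and 6000 are illustrative: models are to be developed in group A (10 000 patients), at first separately for screening and other patients. Severity is minor. This is an exploratory secondary analysis and does not affect the primary model for advanced adenoma or colorectal cancer.

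**What to change.** Reword the sentence so that the target is the number of adenomas, and likewise of polyps. Compare a zero-inflated or hurdle negative binomial with a plain negative binomial on out-of-sample log score and on observed against predicted counts, and adopt the extra zero component only if it does better. Keep logistic regression for the presence of any adenoma. Describe the expected pattern as many zeros with some high counts, and leave open whether overdispersion or zero inflation explains it.

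The cost is one changed sentence, carried into the analysis plan, and one extra comparator model. No new data are needed.

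### The detectable odds ratio of 1.13 does not follow from the protocol's own formula and inputs, which give 1.42; with the stated standard error, power at 1.13 is about 16%, not 80%

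*Protocol article*

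**What the plan says.** The section *Statistical analysis and sample size* of the protocol article treats the 6000 biosample patients in two steps.

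- **Basis for 6000.** The number is attributed to the rule N = 10(k/p), where k is the number of covariates and p the smaller outcome proportion. The section gives no value for either.
- **Detectable effect.** A second formula, N = 8V/β², is given for "80% power and 5% level of significance". Here β stands for ln(OR), and V for the variance that the covariates contribute in the logistic model. The text then says: "This formula can be rearranged to determine the minimum odds ratio that can be detected at a sample size of 6000 with sufficient power". The one further input is introduced by "Assuming a moderate standard error in the regression", with SE = 0.125, and V is obtained as (SE√N)².

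The conclusion is that "the study will have sufficient statistical power to detect an effect with a small effect size with an odds ratio of 1.13".

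The exponents on β and on the bracket are flattened in the extracted text. They are read here as squares, which is the only reading consistent with the constant 8.

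**The concern.** A detectable effect at 80% power and two-sided 5% significance must lie about 2.8 standard errors from zero. The natural log of 1.13 is 0.122, slightly less than one standard error when SE is 0.125, so the claim of sufficient power cannot be right on the stated inputs. Taking V from an assumed SE and from N itself is also circular: the sample size drops out of the answer.

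This is the only detectable effect that the protocol quantifies. It tells readers that the study is powered for a small effect, when the stated inputs support only a larger one. If the figure carries over into the analysis plan and the reports, a weak predictor that is dropped or not significant, including a microbiome summary entered into the risk model, could be read as evidence of no association when the calculation gives no such assurance.

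**Working it through.** **Inputs, all from the section *Statistical analysis and sample size*:** N = 6000; SE = 0.125; power 80%; significance 5%; N = 8V/β²; β = ln(OR); V = (SE√N)². Sidedness is not stated. The constant 8 approximates (1.960 + 0.842)² = 7.85, the two-sided value; the one-sided constant would be 6.18.

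**1. Rearranging as the protocol describes**

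- V = 0.125² × 6000 = 93.75
- β² = 8V/N = 8 × 93.75/6000 = 0.125
- β = √0.125 = 0.3536
- OR = exp(0.3536) = **1.42** (also 1.42 with 7.85 in place of 8)

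**2. Trying to reproduce 1.13**

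| Reading | OR |
|---|---|
| Two-sided, 80% power | 1.42 |
| One-sided, 80% power | 1.36 |
| Two-sided, 90% power | 1.50 |
| Two-sided, 50% power | 1.28 |
| V misread as SE√N, unsquared | 1.12 |
| exp(0.125) | 1.13 |

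Only exp(0.125) returns the stated figure. Because SE is 1/8, 0.125 is both SE and 8 × SE² (= β²). The slip may therefore be a dropped factor of √8 or a square root not taken. The text cannot show which, and the result is the same.

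**3. Power at OR 1.13 with SE = 0.125**

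- z = ln(1.13)/0.125 = 0.1222/0.125 = 0.978
- Two-sided: Φ(0.978 − 1.960) = 16.3%, or 16.5% counting both tails
- One-sided: 25.2%

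**4. N cancels**

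Substituting V = N × SE² into β² = 8V/N gives β² = 8 × SE².

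| N | V | β² | OR |
|---|---|---|---|
| 600 | 9.375 | 0.125 | 1.42 |
| 6000 | 93.75 | 0.125 | 1.42 |
| 60 000 | 937.5 | 0.125 | 1.42 |

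**5. What 1.13 would require**

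- At 80% power: SE = ln(1.13)/√8 = 0.043, about a third of the assumed value.
- Holding V at 93.75: N = 8 × 93.75/0.1222² ≈ 50 200.

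**6. A calculation in which N counts (illustration only)**

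Take SE = 1/√(N·p(1−p)·var(x)) and OR = exp(√8 × SE), with x uncorrelated with the other predictors. Here var(x) is 1 for a continuous predictor per SD, 0.2 × 0.8 = 0.16 for a binary factor held by 20%, and 0.1 × 0.9 = 0.09 for one held by 10%. The protocol gives neither the prevalence p of advanced adenoma or cancer nor the stratum sizes. The values of p below and the 3000-patient stratum are assumptions.

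| N | p | Per SD | Binary, 20% | Binary, 10% |
|---|---|---|---|---|
| 6000 | 5% | 1.18 | 1.52 | 1.75 |
| 6000 | 10% | 1.13 | 1.36 | 1.50 |
| 6000 | 20% | 1.10 | 1.26 | 1.36 |
| 3000 | 5% | 1.27 | 1.81 | 2.20 |
| 3000 | 10% | 1.19 | 1.54 | 1.78 |
| 3000 | 20% | 1.14 | 1.38 | 1.54 |

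Example: N = 6000, p = 10%, per SD gives SE = 1/√(6000 × 0.09) = 0.043 and OR = exp(0.1217) = 1.13.

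**The case against.** The arithmetic cannot be defended, but four points bear on how far it reaches.

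- **The 6000 rests elsewhere.** The protocol bases it on the 10(k/p) rule and uses the second formula only to describe what 6000 can detect. This stands: the error leaves the stated basis for recruitment untouched.
- **The 16% depends on SE = 0.125.** That value is only an assumption, and the fault may lie in it as much as in the odds ratio. This stands too. At N = 6000 and an assumed 10% prevalence, 1.13 per SD is detectable for an uncorrelated continuous predictor. That standard error (0.043) is not the one the protocol states, though, and binary predictors come nowhere near 1.13 over the range shown.
- **The study is exploratory and builds a prediction model.** It will be judged mainly on discrimination, calibration and internal validation, and no single-predictor test hangs on 1.13. The canonical correspondence analysis of the microbiome lies outside this formula altogether. This lowers the stakes, and over-reading of null results is a risk rather than something the protocol plans. It does not make a published power figure correct.
- **Detail can wait for the analysis plan.** Fair for a full recalculation. But the protocol itself states this figure, so correcting it is not a matter of missing detail.

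**Conclusion.** The concern holds. On the protocol's stated formula and inputs the detectable odds ratio is 1.42, not 1.13. If the standard error is 0.125, power at 1.13 is about 16% two-sided, or about 25% one-sided, against the 80% stated. The two-sided reading is inferred from the constant 8.

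Separately, the derivation does not depend on N, so it cannot support any statement about 6000 patients, even with the number corrected.

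The finding does not establish that 6000 is inadequate or that the study is underpowered for small effects in general. Those questions depend on outcome prevalence, on predictor distributions and correlations, and on the sizes of the separate Bowel Cancer Screening Programme (BCSP) and non-BCSP models, none of which enter the stated calculation.

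**What to change.** At a minimum, replace 1.13 with 1.42 if SE = 0.125 is kept, drop the description of the effect as small, and say that the figure follows from the assumed standard error and not from N.

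The better change is to delete the SE-based derivation. In its place:

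- state an assumed prevalence of advanced adenoma or cancer, with a range;
- compute V from that prevalence and the predictor's distribution, allowing for correlation with other predictors;
- report the detectable odds ratio per SD for continuous predictors and for binary predictors at stated frequencies;
- do this separately for the BCSP and non-BCSP models, since the protocol develops these first and each will contain fewer than the 6000 biosample patients.

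The full statistical analysis plan is still to be written, so the recalculation can go there, with the figure corrected wherever the protocol's claim is repeated.

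The cost is text only. The stated figure becomes less favourable if SE = 0.125 is kept, and no endpoint, analysis or recruitment target changes.
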